### Outcomes

Data presented in Table 1 will be measured in the study.

**Table 1 Tab1:** Study measures to be collected

Measure	Instrument	t_0_	t_1_	t_2_	t_3_	t_4_
Primary outcome measure						
Activities of daily living (ADL)	KOOS/HOOS subscale ADL (self-reported)	x				x
Secondary outcome measures						
Pain, symptoms, Sport & Rec and quality of life	KOOS/HOOS subscales pain, symptoms, Sport & Rec and quality of life (self-reported)	x				x
Pain at rest	NRS (self-reported)	x	x	x	x	x
Pain during activity	NRS (self-reported)	x	x	x	x	x
Preoperative anxiety and depression	HADS (self-reported)	x	x			
Other measures						
Usage metrics	number of user sessions, length of time participants interact with the app, content they engage with, frequency of recording self-monitoring parameters, number of awards	continuous recording				
Physical activity	IPAQ (self-reported)	x				
Social support	questionnaire (self-reported)					x
Physician visits post-surgery	questionnaire (self-reported)					x
Use of pain medication	medical record, questionnaire (self-reported)		x	x	x	x
Sex, age	medical record				x	
BMI (size, weight)	medical record				x	
Operated joint	medical record				x	
OPS, ICD	medical record				x	
Comorbidities	medical record				x	
Duration of hospital stay	medical record				x	
Type and duration of planned and performed rehabilitation programme	medical record, questionnaire (self-reported)				x	x
Complications post-surgery	medical record, questionnaire (self-reported)			x	x	x
Structural data of hospitals						
- Number of beds - Number of joint replacement surgeries performed over the past 12 months - Number of nurses in the orthopaedic departments: nurses, nursing assistants, Pain Nurses, full-time equivalent - Number of physicians in the orthopaedic departments: total number, number of orthopaedic specialists, full-time equivalent - Process quality management data for the care of patients with THR/TKR (documentation forms and guidelines, interprofessional standard operating procedures for analgesic therapy, pain management guidelines, other pain therapy guidelines, standard operating procedures for patients with THR/TKR, special contracts with other facilities and mandatory health insurance companies for structured patient care) - Regular cooperation with institutions of inpatient or outpatient rehabilitation						

*KOOS* knee injury and osteoarthritis outcome score, *HOOS* hip disability and osteoarthritis outcome score, *NRS* numerical rating scale, *HADS* Hospital Anxiety and Depression Scale, *IPAQ* International Physical Activity Questionnaire, *BMI* body mass index, *OPS* “Operationen- und Prozedurenschlüssel” (= key for surgery procedures), *ICD* International Statistical Classification of Diseases and Related Health Problems, *THR* Total hip replacement, *TKR* Total knee replacement

The primary outcome measure of the study will be the activities of daily living (ADL) subscale of the Knee injury and Osteoarthritis Outcome Score (KOOS) [35] and the Hip disability and Osteoarthritis Outcome Score (HOOS) [36]. The extensive subscale comprises a variety of daily activities (17 items). A 5-point Likert-scale is used and converted into a normalized 100-point score with zero indicating the worst possible function [35–39]. KOOS and HOOS were chosen, because both provide measures of the same subscales, but adapted for knee and hip, respectively. They have been shown to have good reliability and validity in patients undergoing joint replacement [35, 40].

Secondary outcomes are the subscales for pain, symptoms, function in sport and recreation and knee/hip-related quality of life of the HOOS and KOOS, the preoperative anxiety, measured by the Hospital Anxiety and Depression Scale (HADS) [41, 42] as well as their currently experienced pain at rest and pain during activity measured by an 11 point numerical rating scale (NRS; 0 “no pain” – 10 “maximum pain”).

Other measures collected by self-administered questionnaires and further information registered by the medical record include physical activity measured by the International Physical Activity Questionnaire (IPAQ) [43], social support at recovery, post-surgical physician visits, use of pain medication, sex, age, BMI (body mass index; size, weight), operated joint, OPS (“Operationen- und Prozedurenschlüssel” – key for surgery procedures), ICD (International Statistical Classification of Diseases and Related Health Problems), comorbidities, duration of hospital stay in days, type and duration of planned and performed rehabilitation programme and complications post-surgery.

In the intervention group, app use will be monitored throughout the intervention period. This will include the number of user sessions, length of time participants interact with the app, content with which they engage, frequency of recording self-monitoring parameters and number of awards achieved through the gamification system.

For comparability and detailed description of the study sites, structural data of the participating hospitals are also being assessed. Collected data include information on the number of beds, number of joint replacement surgeries performed over the past 12 months, number and full-time equivalents of nurses, nursing assistants, pain resource nurses, physicians and specialists of the orthopaedic department as well as process quality data for the care of patients with THR/TKR and rehabilitation procedures.

### Data collection procedures

Self-reported measures will be collected via self-administered patient questionnaires. Medical data will be transferred from the patients’ medical record into a medical questionnaire by the project coordinators or study nurses.

In total there will be 5 collection points for the patient data presented in Table 1: baseline (4–6 weeks before surgery, t_0_), the day of admission to the hospital (t_1_), the 1st postoperative day (t_2_), the 7th postoperative day (t_3_) and 3 months post-surgery (t_4_).

Patients whose preoperative consultation and recruitment takes place more than 6 weeks before day of surgery will perform the patient survey at baseline (t_0_) via online survey on their own computer at home. Data collection of patients whose preoperative consultation does not exceed 6 weeks before surgery as well as data collection t_1_, t_2_, and t_3_ will be carried out via online survey on tablet PCs in the hospitals provided by the research team.

The follow-up measure (t_4_) will also be an online-based patient survey, for which the patients will receive a link via e-mail as well as a reminder by post 3 months post-surgery. The e-mail address as well as the postal address of participants will be stored in a separate database.

All data of the participating patients will be pseudonymised using ID allocation. Data are accessible to the project team and exported for analysis only after pseudonymisation.

Structural hospital data will be assessed before the collection of patient data by the project team.

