## Methods/design

### Design

This study is an unblinded, non-randomized, multi-centre (4 sites), double-arm, controlled trial with 1:1 assignment. The duration of the study is 3 years and includes literature review, development of the app, clinic and patient recruitment, intervention delivery, as well as, data collection and analysis.

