**Fig. 1 Fig1:**
[figure not shown]
Flow chart of participants in the pabee study

A random assignment of the participants and simultaneous treatment of intervention and control group would carry the risk that people in the control group might learn about the app and its contents from patients of the intervention group. In order to prevent diffusion of treatment effects among participants, patients scheduled for preoperative consultation from January 2019 to May 2019 will be assigned to the control group and patients scheduled for preoperative consultation from June 2019 to October 2019 will be assigned to the intervention group.

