### Data analysis

Baseline data, clinical and demographic characteristics will be presented to show the baseline comparability of the intervention group and the control group. The analysis will include all patients following the intention-to-treat principle, drop-out and loss to follow-up will be described. Data will be checked for completeness and normality. The treatment effect will be evaluated by the change in ADL using between group analyses, such as independent t-test and ANCOVA to adjust for demographic factors such as age, sex, BMI (body mass index), baseline pain, anxiety, joint, comorbidities, physical activity, pain medication, type and duration of rehabilitation and social support on change in outcomes. For comparison within groups paired t-tests will be conducted. Within the intervention group the relationship between usage metrics and patient reported outcomes will be analysed using linear regression analyses.

All statistical analyses will be performed using IBM SPSS Statistics for Windows, version 24 (IBM Corp., Armonk, N.Y., USA).

Results of the study will be presented at conferences and placed in journals.

The controlled trial will be accompanied by multi-perspective qualitative research approaches to understand user decisions and long-term user engagement of the intervention. These studies will be reported elsewhere.

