## Discussion

The aim of the study is to enhance patient reported outcomes after surgical hip or knee replacement by using mHealth with evidence-based content and interface.

It seems reasonable to bring patient education to the next level and adapt it to the needs and conditions of modern society. In recent years, the concepts of eHealth (Electronic Health) and mHealth have become increasingly important in patient-centred health care aiming to enhance patient involvement and self-management capabilities [19, 20]. mHealth intends to capitalize on people’s ubiquitous access to mobile phones to provide 24/7 health care [51]. Ideally, it leads to improved health outcomes by increasing patient knowledge, providing social support, enhancing patient-provider communication and saving resources at the same time [52].

However, there is a lack of evidence for the effectiveness of the use of mHealth in patients undergoing joint replacement [53, 54]. This study will investigate the effects of an evidence-based mobile app as an educational intervention on patient reported outcomes of this target group.

Numbers of joint replacements are increasing and shorter hospital stays require solid self-management skills. Evidence supporting the use of mHealth to potentially improve patient outcomes is of particular importance to open up new possibilities for patient care.

A major limitation of the study is the non-randomized assignment of participants. Therefore the comparability of the groups regarding all relevant patient characteristics will be comprehensively analysed.

A second limitation is a potential mode effect due to different survey modes (online based vs. tablet based) at baseline and 3 months post-surgery.

Another limitation and potential source of bias is the exclusion of participants assigned to the intervention group, but who failed to download or access the app. We have chosen to do this because those participants miss out on engaging with app contents for the preoperative phase that are expected to have an effect on primary and secondary outcomes. We will, however, analyse and report patients’ reasons for not engaging and consider this aspect regarding the generalisability of our findings.

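### Baseline ADL is collected by hospital tablet or by home online survey according to the wait for surgery, and no adjustment for this is named; if mode matters and the two calendar cohorts differ in waiting time, the between-arm difference in ADL change could be modestly biased.

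*Protocol article*

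**What the plan says.** All places are in the protocol article.

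- **Baseline mode (Data collection procedures).** Patients whose consultation and recruitment fall more than 6 weeks before surgery "will perform the patient survey at baseline (t_0_) via online survey on their own computer at home". For patients with a shorter interval, baseline collection "will be carried out via online survey on tablet PCs in the hospitals provided by the research team".
- **Three-month mode (same section).** One rule for all: "The follow-up measure (t_4_) will also be an online-based patient survey, for which the patients will receive a link via e-mail".
- **Assignment (Participants and recruitment, text after Fig. 1).** "patients scheduled for preoperative consultation from January 2019 to May 2019 will be assigned to the control group". Those seen in the following five months, June to October, form the app arm.
- **Analysis (Data analysis).** "The treatment effect will be evaluated by the change in ADL using between group analyses, such as independent t-test and ANCOVA". The adjustment factors named are age, sex, BMI, baseline pain, anxiety, joint, comorbidities, physical activity, pain medication, rehabilitation and social support. Survey mode and waiting time are not among them, although the list is given as examples and is not closed.
- **Disclosure (Discussion).** "A second limitation is a potential mode effect due to different survey modes (online based vs. tablet based) at baseline and 3 months post-surgery". No analysis is attached to this statement.

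**The concern.** The primary comparison uses change from baseline. If a tablet in the hospital draws a different ADL answer from an online form at home, the difference enters the baseline value and passes into the change score. The rule that decides who gets which mode is the wait for surgery.

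In a randomised trial the tablet/home mix would be balanced in expectation, and a mode effect would only add noise. Here the arms are January–May and June–October cohorts. The description "double-arm, controlled trial with 1:1 assignment" sets the ratio of the arms and says nothing about their composition. If theatre capacity or referral patterns shift over the year, the share of patients waiting more than 6 weeks can differ between arms, and part of any difference in ADL change could then reflect how baseline was measured. The same reasoning applies to the other KOOS/HOOS subscales and to the two NRS pain scores, which are also taken at baseline and 3 months.

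The Discussion treats mode as a general limitation. It does not note that mode is tied to waiting time and so possibly to arm.

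**Working it through.** **1. The plan's own scale.** Sample size gives a 10-point target difference, SD 15, power 0.80, α 0.05, 58 patients per joint and 160 in total. A one-sided two-sample t-test needs 28.5, so 29 per arm, or 58 per joint. With the losses multiplied, 2 × ceil(58 / (0.80 × 0.95 × 0.96)) = 2 × 80 = 160. Both figures reproduce. The match at 58 needs a one-sided test, which the text does not state; that is a separate matter. These inputs are used here only to give the bias a scale.

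**2. How a mode effect reaches the contrast.** Let d be the amount by which a baseline ADL answer on the tablet exceeds the answer the same patient would give at home. Let h be the share of an arm answering baseline at home. The 3-month mode rule is the same for all, so, other things equal:

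bias in (app change − control change) = d × (h in app arm − h in control arm)

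The sign may go either way. This is the bias in the unadjusted t-test. The ANCOVA removes it only as far as its covariates happen to track mode.

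**3. Size under assumed inputs.** The article gives neither d nor the shares. Assuming d of 1, 3 or 5 points and a difference in home share of 10, 30 or 50 percentage points:

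| Difference in home share | d = 1 | d = 3 | d = 5 |
|---|---|---|---|
| 10 points | 0.1 | 0.3 | 0.5 |
| 30 points | 0.3 | 0.9 | 1.5 |
| 50 points | 0.5 | 1.5 | 2.5 |

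That is 1% to 25% of the 10-point target. With d = 0 or equal shares it is zero.

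**4. Against sampling error.** The standard error of the between-arm difference is 15 × √(2/n): 3.9 points with 29 per arm (one joint) and 2.8 with 58 per arm (joints pooled). The largest bias in the table, 2.5 points, is 2.5/3.9 = 0.6 and 2.5/2.8 = 0.9 standard errors respectively.

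**5. Effect on the false-positive rate.** With a two-sided 5% test and the normal approximation, the rate is 1 − Φ(1.96 − b/SE) + Φ(−1.96 − b/SE), where b is the bias.

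| Case | b | 29 per arm | 58 per arm |
|---|---|---|---|
| d = 3, 30 points | 0.9 | 5.6% | 6.2% |
| d = 5, 50 points | 2.5 | 9.7% | 14.6% |

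**6. Can mode alone imitate the target?** A spurious 10-point difference would need, for example, a 10-point mode effect with one cohort answering entirely at home and the other entirely on tablets.

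**The case against.** The strongest case on the other side has five parts.

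- **No evidence of either ingredient.** A reader might infer that a waiting-time difference between cohorts will turn into an apparent app effect. The document does not support that. It needs a real mode effect and an unequal mix, and neither is shown. This stands, and the point is conditional for that reason.
- **The contrast is weak.** Both baseline modes are self-administered online questionnaires; only device and place differ. This also stands and makes the upper end of the assumed range less likely. The authors nevertheless list the effect as a limitation.
- **Home patients may change device too.** A reader might infer that only tablet patients switch mode. The article does not establish this, because the 3-month link is not tied to any device and every participant owns a smartphone. The bias formula does not need it: what matters is the tablet/home difference at baseline. Baseline mode would not, however, capture device differences at 3 months.
- **It is disclosed and the covariate list is open.** Both are true, so adjustment is not excluded, and a separate analysis plan might contain it. What remains is that the article sets the mode rule, concedes the effect and names its adjustment factors without connecting them. The comparison of groups promised in the Discussion concerns patient characteristics, and Table 1 lists neither mode nor waiting time.
- **Mode cannot be separated from a long wait.** Correct: under the rule they are the same indicator, so its coefficient is not a pure mode effect. For the comparison of arms this does little harm, since both are settled before the app is handed over and a long-wait imbalance is also worth adjusting for.

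**Conclusion.** The point holds in conditional form and is minor. The plan ties baseline mode to waiting time, compares calendar cohorts on change from baseline, acknowledges a possible mode effect and names no adjustment for it. A bias follows only if mode shifts ADL answers and the cohorts differ in waiting-time mix. On assumed values of 1 to 5 points and 10 to 50 percentage points it is 0.1 to 2.5 points, below one standard error throughout and at most a quarter of the target difference. It would not by itself overturn a clear 10-point result, but it could matter to a borderline one.

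**What to change.** 1. Record the baseline mode actually used, and report the tablet/home split by arm with the baseline characteristics.
2. Add baseline mode (tablet or home online) as a binary covariate in the ANCOVA of change in ADL, and in the models for the other outcomes measured at baseline and 3 months (remaining KOOS/HOOS subscales, NRS pain at rest and during activity).
3. State that the adjusted estimate, not the unadjusted t-test, is the main result.
4. State that the term adjusts for mode and a wait of more than 6 weeks together and is not to be read as a mode effect.

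The cost is one degree of freedom per model and a sentence or two of text. No new patient measurement is needed, because under the stated rule mode follows from the interval between consultation and surgery. Repeating the comparison within each mode is optional; with about 58 patients per joint, split again by mode, it would have low power.

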### Sample size

Based on the primary outcome ADL subscale of the KOOS/HOOS and the assumable clinical relevant change of 10 points [37, 44, 45], we expect that the group using the mobile app in addition to the standard care will improve at least 10 points more than the control group after having undergone TKR/THR 3 months post-surgery.

To allow for separate analysis of patients with knee and hip OA, 58 knee patients and 58 hip patients are required to detect a difference of 10 points on the HOOS/KOOS ADL subscale (SD 15, power = 0.80 and α = 0.05) [37, 44, 46]. Allowing for 20% dropout [47–49], 5% complications post-surgery [50] and 4% erroneous records, a total of 160 patients will be recruited.

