### Study hypothesis

The primary aim of the study is to test the hypothesis that patients undergoing TKR/THR using the app RECOVER-E attain better function in activities of daily living 3 months post-surgery when compared to patients undergoing surgery without using the app (control group).

Further hypotheses assume that patients using the app RECOVER-E experience significantly less symptoms, less pain, better function in sport and recreation, as well as a better knee/hip-related quality of life 3 months post-surgery when compared to the control group. Furthermore, we hypothesize less preoperative anxiety and postoperative pain in patients using the app RECOVER-E when compared to the control group.

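### The trial is sized for separate knee and hip analyses but hypothesised and modelled as one combined comparison, and neither the t-test nor the ANCOVA is named as primary

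*Protocol article*

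**What the plan says.** Three sections of the protocol article bear on what the primary analysis is.

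- **Study hypothesis.** The primary aim is to "test the hypothesis that patients undergoing TKR/THR using the app RECOVER-E attain better function in activities of daily living" at 3 months. Knee and hip patients appear together in a single hypothesis. The opening paragraph of the Sample size section also states the expected 10-point advantage for both procedures together.
- **Sample size.** The only calculation given is per joint. Its stated purpose is "To allow for separate analysis of patients with knee and hip OA". It arrives at 58 patients per joint for a 10-point difference in the ADL score, under "SD 15, power = 0.80 and α = 0.05". It states neither the sidedness of the test nor any division of α between the joints.
- **Data analysis.** The effect on change in ADL is to be assessed by "between group analyses, such as independent t-test and ANCOVA". Joint is one of the ANCOVA adjustment factors. Separate knee and hip analyses are not described, and neither method is called primary.

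**The concern.** Within a knee-only or hip-only analysis, joint is a constant and cannot serve as a covariate. The ANCOVA as described therefore has to combine the joints, as the hypothesis does. The sample size rests on a different analysis, two stand-alone tests. The protocol thus fixes two bases for the primary result and does not connect them.

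The choice of method adds to this. Assignment is by calendar period (control patients first, intervention patients afterwards), and the Discussion calls the lack of randomization a major limitation. An unadjusted t-test takes no account of differences between the two cohorts, whereas the ANCOVA adjusts for measured ones, so the two can disagree.

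At stake are the error rate if more than one result may carry the claim, the power if both joints must succeed, and the credibility of the main result if an unadjusted comparison decides it.

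**Working it through.** **Inputs from the protocol article.** Difference 10 points, SD 15, power 0.80, α = 0.05 and 58 patients per joint (Sample size); "double-arm, controlled trial with 1:1 assignment" (Design), hence 29 per arm per joint and 58 per arm overall (116 evaluable). Losses are 20% dropout, then "5% complications post-surgery [50] and 4% erroneous records, a total of 160 patients will be recruited" (Sample size).

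**1. Reproducing 58 per joint.** Per arm, n = 2 × (15/10)² × (z_α + z_power)².
- One-sided 5%: 4.5 × (1.645 + 0.842)² = 27.8, so 28 per arm. The exact t-test solution is 28.52, so 29 per arm, or **58 per joint**. This matches.
- Two-sided 5%: 4.5 × (1.960 + 0.842)² = 35.3, so 36 per arm (72 per joint). The exact t-test solution is 36.31, so 37 per arm (74 per joint). This does not match.
- Recruitment: 116 / (0.80 × 0.95 × 0.96) = 116 / 0.7296 = 159.0, in line with 160.

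The stated size is therefore a stand-alone one-sided 5% test in each joint, with no allowance for there being two.

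**2. Power with 29 per arm (t-test).** One-sided 0.806; two-sided 0.704.

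**3. What follows under each possible decision rule.** The protocol states none of these rules.

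| Rule | Consequence |
|---|---|
| Knee or hip suffices, one method | False-positive chance 1 − 0.95² = 9.75% |
| Knee, hip or combined suffices, t-test only | About 10.5% to 11.7% (simulated) |
| Combined only, t-test or ANCOVA | About 6.4% to 7.7% (simulated) |
| Any of the six (knee, hip, combined, each by t-test and ANCOVA) | About 14% to 17% (simulated); 16% two-sided at correlation 0.5 |
| Both joints must succeed | Power 0.806² = 0.65 one-sided; 0.704² = 0.50 two-sided |

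The 9.75% needs only that knee and hip patients are different people. The simulated figures come from 10,000 null data sets per scenario, 29 per arm per joint, with an assumed baseline-to-outcome correlation of 0.3 to 0.7, one- and two-sided tests, an ANCOVA adjusted only for baseline ADL (plus joint when combined), and no confounding.

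**4. One combined test on the same patients.** With 58 per arm the standard error is 15 × √(2/58) = 2.785, and 10/2.785 = 3.590.
- Two-sided: Φ(3.590 − 1.960) = Φ(1.630) = 0.948.
- One-sided: Φ(3.590 − 1.645) = Φ(1.945) = 0.974.

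**5. The alternative of two confirmatory joint-specific tests.** With α halved to 0.025 each and a two-sided t-test, 45 per arm are needed, or 180 evaluable and 180/0.7296 = 247 recruited. One-sided, 37 per arm are needed, or 148 evaluable and 148/0.7296 = 203 recruited.

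**The case against.** The strongest reply is that the text already points to one primary claim. There is one hypothesis, one primary outcome row in Table 1, one expected effect for both procedures, and joint as a covariate. On that reading the separate-analysis phrase is permissive: the trial is made large enough that each joint can also be examined, which is generous for a combined test. The t-test and ANCOVA would be ordinary unadjusted and adjusted reporting. The hierarchy of tests is something an article may leave to an analysis plan that is not shown here.

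Much of this stands. Nothing in the protocol calls knee and hip co-primary, and nothing says the t-test will decide. A reader might infer that the 5% error rate is already breached, or that the claim has several chances to succeed. The documents do not support that, because each inflated error rate and each reduced power needs a decision rule that they do not contain. The simulated rates also leave out confounding, so they do not describe this trial's actual error.

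What remains is not simply detail deferred to a later document. The only power calculation is for analyses that the Data analysis section does not describe, and the analysis implied by the hypothesis and covariate list has no stated power. If the joint-specific analyses are supportive, a sentence saying so would resolve that part. The open-ended choice between an unadjusted and an adjusted method would still need settling in a design with sequential, non-randomized cohorts.

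**Conclusion.** The concern holds as an inconsistency within the protocol and as a conditional risk, not as a demonstrated error. The sample size describes two joint-specific tests; the hypothesis and covariate list describe one combined test; neither method is primary. That the model is combined is an inference, though a firm one, since the protocol never says so outright.

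Depending on the rule eventually adopted, the false-positive chance could lie anywhere from 5% (one named test) to about 16% (any of six), or power could fall to 65% or 50% (both joints). These figures take the difference of 10 and SD of 15 at face value; the 16% also assumes a correlation of 0.5. The point should be settled before the analysis. It is cheap to settle, because the combined test is already well powered at the planned size.

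**What to change.** **In Data analysis**, name one primary test: the pooled ANCOVA of ADL at 3 months (t4) on arm, two-sided at 5%, adjusted for baseline (t0) ADL, joint and those listed patient characteristics that precede treatment. These include age, sex, BMI and comorbidities. Table 1 has them extracted from the record at t3, but they describe the patient before treatment and should not be dropped for that reason. Baseline ADL is collected but is not among the listed covariates. With it in the model, analysing the t4 score or the change from t0 gives the same arm effect, so the stated interest in change is preserved.

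Report knee and hip estimates with confidence intervals from an arm-by-joint interaction as supportive results, and the t-test as an unadjusted description.

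**In Sample size**, state that 116 evaluable patients give the pooled test about 95% power two-sided for 10 points with SD 15. State also that each joint alone has about 70% power two-sided, and 80% only one-sided.

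**Cost.** Wording only, with no more patients. The downside is that no confirmatory claim can be made for knee or hip alone. If such claims are wanted with α split between the joints, recruitment would have to rise to about 247 two-sided, or about 203 one-sided.

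### The 80% power claimed for 58 patients per joint holds only for an undeclared one-sided 5% test; with a two-sided test the separate knee and hip analyses have about 70%

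*Protocol article*

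**What the plan says.** The Sample size section of the protocol article sets the size for each joint separately. It opens the calculation with "To allow for separate analysis of patients with knee and hip OA" and then states that "58 knee patients and 58 hip patients are required to detect a difference of 10 points on the HOOS/KOOS ADL subscale", under "SD 15, power = 0.80 and α = 0.05". The expected effect is that app users "will improve at least 10 points more than the control group". The total is then raised to 160 for 20% dropout, 5% complications and 4% erroneous records.

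The Design section describes a "non-randomized, multi-centre (4 sites), double-arm, controlled trial with 1:1 assignment". The Data analysis section evaluates the change in ADL "using between group analyses, such as independent t-test and ANCOVA", and lists the joint among the adjustment factors. The Study hypothesis section is worded in one direction: app users are to "attain better function in activities of daily living 3 months post-surgery when compared to patients undergoing surgery without using the app".

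None of these sections says whether α is one-sided or two-sided.

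**The concern.** An unqualified α of 0.05 beside an independent t-test is ordinarily read as two-sided. On that reading, a standardised difference of 10/15 calls for clearly more than 29 patients per arm, so a reader would credit each joint-specific analysis with power that it does not have. The risk of missing a true 10-point effect in knees, or in hips, would be about 30% and not the 20% stated.

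If a one-sided 5% test was meant, the power figure is right, but the trial then works at the equivalent of a two-sided 10% level without saying so. Leaving this open also allows the sidedness to be settled after the data are seen, which matters in an unblinded, non-randomised trial.

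**Working it through.** **Inputs.** Difference 10, SD 15, power 0.80, α 0.05 and 58 patients per joint (Sample size); 1:1 assignment (Design). The standardised difference is d = 10/15 = 0.667. I assume that 1:1 holds within each joint, so n = 58/2 = 29 per arm.

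**Is 58 the total per joint or the number per arm?** Two joints give 2 × 58 = 116 evaluable patients. Applying the three stated losses in turn: 116 / (0.80 × 0.95 × 0.96) = 116 / 0.7296 = 159.0, which matches the stated 160. If 58 were per arm within each joint, 232 evaluable patients would be needed, and 232 / 0.7296 = 318, far from 160. So 58 is the total per joint.

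**Reproducing the plan's figure.** The normal approximation is n per arm = 2 (z_α + z_β)² / d², with z_β = 0.842.

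- One-sided 0.05: 2 × (1.645 + 0.842)² / 0.667² = 27.8, so 28 per arm (56 per joint). The exact noncentral-t calculation gives 28.5, so 29 per arm, which is 58 per joint. This is the plan's number exactly.
- Two-sided 0.05: 2 × (1.960 + 0.842)² / 0.667² = 35.3, so 36 per arm (72 per joint). The exact calculation gives 36.3, so 37 per arm (74 per joint). Neither is 58.

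**Power with 29 per arm.** The noncentrality is d × √(n/2) = 0.667 × √14.5 = 2.54, on 56 degrees of freedom.

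| Test at α 0.05 | Critical t | Power for 10 points |
|---|---|---|
| One-sided | 1.673 | 80.6% |
| Two-sided | 2.003 | 70.4% |

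The normal approximation gives 81.4% and 71.9%, so the gap does not depend on the method. With 29 per arm and a two-sided test, 80% power is reached at a difference of 11.2 points.

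**Pooled comparison.** With both joints together there are 58 per arm. The noncentrality is 0.667 × √29 = 3.59, on 114 degrees of freedom. Two-sided power for 10 points is 94.5%, and 80% power is reached at 7.9 points.

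**Size needed for 80% two-sided power per joint.** 2 × 74 = 148 evaluable patients, and 148 / 0.7296 = 203 recruited, against the planned 160.

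**The case against.** The strongest reply is that nothing has been miscalculated. The figure of 58 is exactly right for a one-sided 5% t-test, the hypothesis and the expected effect are both worded in one direction, and the article never says two-sided. It is right that this is not an arithmetic slip. But a directional hypothesis does not declare a one-sided test, and the analysis section gives no one-sided criterion.

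A second reply is that a journal article condenses the full protocol, where the sidedness may be given. That would excuse silence. Here the article prints a specific number beside a specific power and α, and a reader who takes α in the usual way is misled by it.

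A third reply is that ANCOVA would recover the loss. If the covariates correlated 0.5 with the outcome, the residual SD would be 15 × √(1 − 0.25) = 13.0 and two-sided power per joint would be about 82%. The article gives no such correlation, does not use one in the calculation, and also plans the unadjusted t-test. The gain is possible but cannot support the stated 80%.

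A fourth reply largely stands. The primary hypothesis covers knee and hip patients together, and using joint as a covariate makes sense only in a pooled model. On that reading the primary comparison is well powered even with a two-sided test.

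A reader might infer two stronger conclusions. One is that the trial as a whole is underpowered for 10 points; the pooled figure of 94.5% contradicts this. The other is to multiply the two joint-specific powers and fault the trial for a low chance of success in both joints; no section requires both to succeed, so that product answers no question in the plan.

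**Conclusion.** The point holds as an undeclared condition behind a stated power. The claim of 80% at α 0.05 with 58 patients per joint is true for a one-sided 5% test (80.6%) and untrue for a two-sided one (70.4%), a shortfall of about 10 percentage points. It affects the separate knee and hip analyses, which are the article's stated basis for the sample size. It does not threaten the pooled comparison to which the primary hypothesis and the ANCOVA point.

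The conclusion rests on equal arms within each joint, the stated SD of 15, an unadjusted t-test, and losses no larger than those assumed. Two-sided testing is the ordinary reading of the text, but it is the reader's inference, since the article leaves the matter open.

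**What to change.** Keep 160 patients. In the Sample size section, state whether α 0.05 is one-sided or two-sided, and in the Data analysis section commit to the same sidedness for the t-test and the ANCOVA.

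- If two-sided: restate the power of each joint-specific analysis as about 70% for 10 points (80% for 11.2 points), and add that the pooled comparison of 58 per arm has about 94.5% power for 10 points. The pooled figure supplements the reason given for the size; it need not replace it.
- If one-sided 0.05 was intended: declare it before results are known. The figures 58 and 80% may then stand.

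Either way the cost is one reworded paragraph, a matching phrase in the analysis section, and no extra patients. The downside of the two-sided option is a less favourable stated power for the separate knee and hip analyses.
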